## Background and rationale {6a}

Cardiovascular diseases are the leading cause of death and a focal contributor to disability. Managing acute myocardial infarction (AMI) has improved significantly over the past years due to progress in both pharmacotherapy and invasive procedures. The mortality rate following AMI varies between countries, but an overall decrease has been observed [1]. Nevertheless, 12% of the patients die within one year after AMI [2]. Therefore, efforts should be made to optimize the cardiac rehabilitation process. It is crucial to focus on preventing future ischemic events by providing optimal care for patients at-risk [3]. Secondary prevention aims to control all cardiovascular disease (CVD) risk factors, which may be challenging in everyday practice. Jankowski et al. reported that only 2.9% of patients with coronary artery disease (CAD) have all CVD risk factors adequately controlled corresponding to values recommended in the guidelines [4]. Proper CVD risk factor control remains a challenge in the real-world setting.

Several efforts are being made to improve patients’ prognosis. The latest approach to improve cardiac rehabilitation is the use of novel telehealth-based solutions. Over 3.2 billion smartphones are used globally, and the mobile applications market is expected to grow by 18.4% between 2018 and 2026. Therefore, enhancing cardiac rehabilitation by mobile application support may be a promising tool. Telemedicine has proved to be an effective solution in clinical scenarios. Widmer et al. demonstrated that augmentation of usual cardiac rehabilitation with an online and smartphone-based program improved CVD risk factor management and reduced rehospitalizations or emergency department visits by 40% (*p*<0.05) [5]. Naturally, not all cardiac patients are capable of using smartphones. Gallagher et al. reported that 54.6% of cardiac patients eligible for attending cardiac rehabilitation used technology for health purposes. Patients used it to access information on health conditions and medications mainly [6]. Coorey et al. concluded in the meta-analysis that mobile applications have a beneficial influence on CVD risk factors control, but more scientific evidence is required to enhance the implementation of telemedicine into clinical practice [7].

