### Outcomes {12}, Participant timeline {13}, Plans to promote participant retention and complete follow-up {18b}

All 100 patients will be observed for 6 months after discharge. The endpoints will be assessed twice, during two control visits, in 1- and 6-months, after enrollment. Patients will be called to schedule the control visit’s date after discharge. Additionally, patients in the IG will receive a notification in their mobile app reminding them about the upcoming ambulatory visits.

Figure 2 shows the recommended SPIRIT figure with the participant timeline. Primary outcome includes both need for rehospitalization and/or urgent outpatient visit and assessed between baseline and 6-month control visit. There are five secondary outcomes related to cardiovascular risk factors control: blood pressure, body mass, nicotinism, dyslipidemia and need for rehospitalization and/or urgent outpatient visit assessed between baseline and 1-month control visit. Detailed target values regarding risk factors control have been presented in Table 1 based on ESC Chronic Coronary Syndrome guidelines [16]. Each value will be categorized as met or not. Secondary outcomes will also include quality of life and depression severity assessment (MacNew, EQ-5D-5L, and DASS-21 questionnaires), cardiovascular risk factors knowledge (CVD risk factors identification recommended BP values, desired lifestyle intervention identification). and return to work in case of professionally active patients.

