### Sample size {14}

Currently, data regarding the achieved reduction of rehospitalizations or prelevance of urgent visits associated with mobile application use remains limited. Most previous studies were conducted on smaller populations. The sample calculation was based on Widmer and colleagues’ [5] study, considering rehospitalization and urgent ambulatory visits—comparing the effects of an online and smartphone-based program with standard rehabilitation on the mentioned endpoint. A 40% decrease in the primary endpoint was observed. Fifty percent of patients in the control group and 20% in the interventional arm were rehospitalized or visited the emergency department.

An online calculator (https://clincalc.com/) was used to determine the sample size, assuming the power of 80% and significance of 5%. A total of 76 patients (38 per group) were required. However, considering a possible lost-to-follow-up group and possible dropouts, a decision to recruit 100 patients was made. The reason for the dropout is lack of consent or inability to attend control visits or consent withdrawal.

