## Statistical methods

### Statistical methods for primary and secondary outcomes {20a}, Methods for additional analyses (e.g. subgroup analyses) {20b}, Methods in analysis to handle protocol non-adherence and any statistical methods to handle missing data {20c}, Interim analyses {21b}

In terms of the endpoints, we will look at the frequency of the events 6 months after the discharge, since we believe that due to randomization the groups will be similar at the beginning. No other (including no interim) analyses will be performed in the present study. Regarding secondary endpoints, the change from baseline will be assessed and the frequency of the events in case of rehospitalizations and/or urgent ambulatory visits after 1 month. The distribution of continuous variables will be estimated using the Shapiro-Wilk test. Continuous variables presented with normal distribution will be presented as mean values and standard deviations (SD). All continuous variables presented non-normal distribution will be demonstrated as median values and interquartile ranges. In the case of variables with a normal and non-normal distribution, the groups will be compared using the Student's t-test and the non-parametric Mann-Whitney U test. The comparison of qualitative variables between the groups will be performed using the Fisher exact test. In order to compare changes in the values of continuous variables over time, the analysis of variance will be performed. To compare the outcome of the patients, the Kaplan-Meier estimators will be utilized. For quantitative variables, the change from baseline will be assessed. Additionally, in order to diminish differences in sex and age related to group size, propensity score matching analysis will be performed as well. We also plan to conduct a subanalysis in the group of patients who attended rehabilitation, as well as in those who did not attend.

A per-protocol analysis will be performed after completing all of the follow-up visits. In the analysis, we will include all patients who meet inclusion criteria and sign informed consent regardless of the follow-up completion. Statistical calculations will be performed twice; after obtaining data from the first follow-up visit from all patients and after the final follow-up, 6 months after discharge. In case of missing data, patients will be excluded from the particular analysis.

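### The analysis is labelled per-protocol but defined as roughly all randomised patients, and the missing-data rule would probably drop non-attenders from the primary comparison

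*Protocol article*

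**What the plan says.** The last paragraph of the Statistical methods section makes three statements about who is analysed.

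- Label: "A per-protocol analysis will be performed after completing all of the follow-up visits".
- Definition: "we will include all patients who meet inclusion criteria and sign informed consent regardless of the follow-up completion".
- Missing data: "In case of missing data, patients will be excluded from the particular analysis".

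Other sections determine what these mean for the primary endpoint.

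- The Outcomes section defines the endpoint: "Primary outcome includes both need for rehospitalization and/or urgent outpatient visit and assessed between baseline and 6-month control visit". Death is not a component.
- The same section says how endpoints are collected: "The endpoints will be assessed twice, during two control visits, in 1- and 6-months, after enrollment".
- On retention, patients in both arms are phoned to arrange their visits, but in addition "patients in the IG will receive a notification in their mobile app reminding them about the upcoming ambulatory visits".
- The Sample size section lists reasons for loss: "The reason for the dropout is lack of consent or inability to attend control visits or consent withdrawal".
- The section on allocation and blinding has eligibility checked and consent obtained before the allocation is revealed.

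**The concern.** In a superiority trial the primary comparison should keep the groups that randomisation created. A per-protocol label on the main analysis points to a selected subset, while the definition after it points to nearly everyone. An analyst could cite the text in support of either population.

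The missing-data rule adds a second problem. If event status is collected at the 6-month visit, a patient who does not attend has none recorded and is left out. Being unable to attend is plausibly related to illness or readmission, which is what the endpoint measures. Attendance may also differ by arm, because only app patients get the extra reminder. Exclusion after randomisation that depends on both arm and outcome can bias the treatment effect, and the trial is open-label.

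**Working it through.** **Step 1. Do the three statements fit together?**

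- Label against definition: they conflict. A per-protocol set needs exclusions for deviations, and the protocol defines none. Because consent and eligibility come before allocation is disclosed, the defined set is approximately all randomised patients.
- Definition against missing-data rule: they can coexist. Everyone belongs to the set, and each analysis uses those with data. That is available-case analysis.
- Consequence for the primary endpoint: assessment takes place at visits, and inability to attend is an expected reason for loss. Available-case analysis of the primary endpoint therefore probably omits non-attenders, who are the patients the definition sets out to keep.

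**Step 2. How many patients could be affected?**

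The plan's inputs (Sample size section) are 50% against 20%, 5% significance (two-sided assumed), 80% power and equal groups. With pooled variance under the null:

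n per group = [1.96·√(2·0.35·0.65) + 0.8416·√(0.5·0.5 + 0.2·0.8)]² / 0.30² = 38.48

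The plan states 38 per group, 76 in total, so its figure reproduces apart from rounding. Recruiting 100 leaves an allowance of 100 − 76 = 24. This is recruitment inflation, not a forecast of losses.

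Normal-approximation power is 89.4% with 50 per arm analysed and 79.5% with 38 per arm. With Fisher's exact test, the plan's test for qualitative variables, it is 85.3% and 73.0%. The allowance addresses power. It does nothing about bias from who is missing.

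**Step 3. What could the missing patients change?**

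Assume the full allowance is used, 12 per arm, with observed rates close to the planning rates.

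| Treatment of the 12 + 12 missing | Control | App | Difference (control − app) | Fisher p |
|---|---|---|---|---|
| Excluded | 19/38 (50.0%) | 8/38 (21.1%) | 28.9 points | 0.016 |
| Missing app patients all events, missing controls none | 19/50 (38%) | 20/50 (40%) | −2 points | 1.0 |
| Missing controls all events, missing app patients none | 31/50 (62%) | 8/50 (16%) | 46 points | <0.0001 |

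The last two rows are limits, not predictions.

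**Step 4. Does the suspected mechanism give a large false benefit?**

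Assume no true effect, 35% risk in both arms. Observed risk = 0.35·(1 − m_event) / [0.35·(1 − m_event) + 0.65·(1 − m_no event)], where m is the proportion missing.

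- Sicker patients lost in both arms, more in control. Control m = 40% and 20%: 0.21/(0.21 + 0.52) = 28.8%. App m = 30% and 10%: 0.245/(0.245 + 0.585) = 29.5%. The false difference is below 1 point, with 50·(1 − 0.73) + 50·(1 − 0.83) = 22 patients lost.
- Opposite patterns in the two arms. Control m = 15.4% and 28.6%: 39.0%. App m = 40% and 15.4%: 27.6%. The false benefit is about 11 points.

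All these proportions are assumptions. A large false benefit appears when the arms lose different kinds of patient. Loss of sicker patients in both arms need not produce one.

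**The case against.** The strongest defence is that only the label is wrong. No per-protocol exclusion is written down, so the label by itself removes nobody, and the inclusion and missing-data sentences together describe ordinary available-case analysis. This stands in part. A reader might infer that the three sentences are mutually incompatible, but only the label and the definition clash.

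Second, the exclusion is triggered by missing data, not by a missed visit. Readmissions and urgent visits can be learned without a visit, and nothing forbids that. This also stands, and it is why the loss of non-attenders is probable rather than certain. The protocol does, however, name visits as the point of assessment and provides no other route.

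Third, a reader might infer that deaths are dropped as missing. The text has no rule for deaths. A patient who dies cannot attend, so exclusion is a likely consequence, but it remains an inference. The background figure, "12% of the patients die within one year after AMI", cannot be turned into an expected number here: the trial excludes patients with life expectancy under 6 months from non-cardiac illness and requires app skills. The Discussion expects no mortality difference between groups, but that is an expectation and not a handling rule.

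Fourth, there are mitigations. Both arms are phoned about visits, and Kaplan-Meier estimators are planned and can use partial follow-up. Both count. But the Kaplan-Meier analysis is neither named as primary nor exempted from the exclusion rule, and censoring at last contact still assumes that loss is unrelated to risk.

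**Conclusion.** The point holds as a conflict between label and definition, together with an available-case rule that probably removes non-attenders from the primary comparison. It should be corrected, because the text supports materially different populations for the main test of a superiority trial.

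The direction and size of any bias are unknown. Under the assumed 12 missing per arm, the bounds run from −2 to +46 points around an observed 28.9. A reader might infer that the plan is likely to create a large false benefit for the app. The documents do not support that: it takes contrasting missingness patterns in the two arms, for which they give no reason, and loss of sicker patients in both arms gave under 1 point in the example above. If every primary outcome were obtained, the bias from exclusion would disappear, but the protocol itself plans for losses. The sample size is not at fault on this point.

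**What to change.** 1. Delete the per-protocol label for the main analysis and state that all randomised patients are analysed in the arm assigned. Any per-protocol analysis is secondary, with its exclusions defined.
2. For patients who miss the 6-month visit, obtain readmission, urgent-visit and vital status by phone or from hospital records, in the same way in both arms.
3. Keep patients with partial follow-up in the planned Kaplan-Meier analysis, censored at last contact.
4. State how deaths are handled, for example by a sensitivity analysis that counts death as an event. The primary endpoint need not change, and changing it this late would be debatable, as would adding new reminders to the control arm.
5. Add a best/worst-case sensitivity analysis for missing primary outcomes.

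The cost is a few phone calls or record checks, a little more analysis, and an amendment through the Ethics Committee, as the Oversight section already provides. Version 3 is dated 21 February 2022, with recruitment due to end about 31 March 2022 and 6 months of follow-up after that, so the change can be made before the final data are complete.

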## Assignment of interventions: allocation, blinding

### Sequence generation {16a}, Concealment mechanism {16b}, Implementation {16c}, Who will be blinded {17a}, Procedure for unblinding if needed {17b}

This is an open-label study. Randomization will be performed with an online tool by an independent statistician available at (www.randomizer.org). A hundred sets will be generated, each with a number (1 for CG and 2 for IG). All allocations to CG and IG will be executed before the study begins. The list of subsequent allocations will not be visible for the recruiting physician until the initial eligibility assessment of the patient and obtaining the patient’s consent for study participation. After collecting the initial documentation, the physician will be unblinded and will receive the group allocation information from the principal investigator. It should be underlined that the person who checks for inclusion criteria and introduces the patient into the trial protocol is blinded until patient agreement. Figure 1 shows the study design flow chart, describing all the steps of the study (Fig. 1). The investigator performing statistical analysis will be blinded, as well as nurses collecting blood samples on the follow-up visits. Taking into consideration the use of the mobile application in everyday practice, it is impossible to blind physicians performing follow-up visits. It could be regarded as ethically doubtful, because based on the data provided via mobile application, clinical decisions can be made (i.e., blood pressure treatment augmentation).

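### The protocol rules out interim analyses but schedules calculations after the 1-month visits, when up to about a third of patients are still in open-label follow-up

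*Protocol article*

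**What the plan says.** All places are in the protocol article.

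- **Statistical methods.** The section excludes further analyses: "No other (including no interim) analyses will be performed in the present study". Its second paragraph sets two rounds: "Statistical calculations will be performed twice; after obtaining data from the first follow-up visit from all patients", and again after the final follow-up. Among the secondary endpoints it lists "the frequency of the events in case of rehospitalizations and/or urgent ambulatory visits after 1 month", and it assigns the Fisher exact test to between-group comparisons of qualitative variables.
- **Outcomes {12}.** "Primary outcome includes both need for rehospitalization and/or urgent outpatient visit and assessed between baseline and 6-month control visit". One of the secondary outcomes is "need for rehospitalization and/or urgent outpatient visit assessed between baseline and 1-month control visit". On duration: "All 100 patients will be observed for 6 months after discharge".
- **Assignment of interventions: allocation, blinding.** The trial is open-label. The investigator doing the statistics is blinded, but "it is impossible to blind physicians performing follow-up visits".
- **Oversight and monitoring.** There is no external monitoring committee, and the principal investigator meets all the researchers every month about progress.

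**The concern.** Calculations run while patients are still being followed are interim in the ordinary sense, so the two statements in the Statistical methods section conflict as written. The 1-month event outcome is also closely tied to the primary outcome. It is the same composite with a shorter window, so each event by month 1 is already a primary-outcome event.

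The setting makes an early look more delicate than usual. One department runs all the control visits, and the physicians who conduct them know the allocation. Staff review app data daily and may advise a patient to attend a clinic or emergency department, so the endpoint depends partly on their judgement. If the early direction of effect became known, it could shift referral, contact with patients, or the recording of urgent visits among those not yet at month 6. A blinded analyst does not limit who later reads the output. A final report that repeated the statement that no interim analysis was done would also be inaccurate.

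**Working it through.** **1. The statements side by side.** One sentence excludes interim analyses. Another sets a first round of calculations once every patient has had the first follow-up visit. The only stated content that fits this date is the set of 1-month outcomes, including the composite event. The sentence does not itself say that the arms are compared. That follows from the between-group tests named in the same section, and no other purpose is given.

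**2. How many patients are still in follow-up at that point?** The plan gives no figure, so there is none to reproduce. The sample size plays no part here.

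Inputs:
- Recruitment runs from 1 December 2020 to about 31 March 2022 (Trial status).
- Accrual is about 7 patients per month (Methods, recruitment paragraph).
- The target is 100 patients, with visits at 1 and 6 months (Outcomes).

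The last 1-month visit falls about 30 April 2022. Patients enrolled in the final 6 − 1 = 5 months of recruitment have then not reached month 6. With uniform accrual at rate r and an analysis lag of L months, the number still in follow-up is r × (5 − L).

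Two values of r are possible, because the stated rate and the dates do not agree exactly: 7 × 16 months = 112, not 100. From the dates, 485 days / 30.4375 = 15.93 months, and 100 / 15.93 = 6.28 per month.

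| Lag L (months; all but 0 assumed) | r = 6.28 | r = 7 |
|---|---|---|
| 0 | 31.4 | 35 |
| 0.5 | 28.2 | 31.5 |
| 1 | 25.1 | 28 |
| 2 | 18.8 | 21 |

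The range is therefore 31 to 35 patients with no lag, and about 19 to 32 with a lag of 0.5 to 2 months.

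**3. How much observation is outstanding?** With no lag, the 5r patients have on average 2.5 months to go. The remaining time is 5 × 6.28 × 2.5 = 78 patient-months, or 5 × 7 × 2.5 = 87.5. Planned follow-up is 100 × 6 = 600 patient-months, so 13% to 15% is outstanding and about 85% to 87% has been observed.

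**4. Does the early look inflate type I error?** Two-sided Fisher tests at 5% with 50 patients per arm were simulated under no effect (20,000 runs per setting). The assumed 6-month event probability was 50% or 35%. The assumed 1-month probability was set by giving month 1 one sixth or one third of the cumulative hazard, which gives 7% to 21%.

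- 6-month test alone: 3.1% to 3.6% false positives.
- At least one of the two tests: 4.1% to 5.9%.

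The 6-month test keeps its own level, because no stopping rule is attached to the first round.

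**The case against.** The strongest reply is that the text can be read coherently. The ban on interim analyses directly follows the sentence on 6-month event frequency, and the next sentence turns to secondary endpoints. On that reading, only an interim analysis of the primary outcome is excluded, and the 1-month outcomes are simply calculated when complete. By then every patient is enrolled and allocated, so recruitment and allocation cannot be affected. The physicians already know each patient's arm and events, and what an aggregate result would add is not quantified. A condensed article may also leave rules on access to results to a fuller document.

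Much of this stands, and it rules out three stronger claims that a reader might infer:

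- **That early results will reach unblinded staff.** The protocol does not say that anyone receives them. It says only that the analyst is blinded, and it states no restriction on the output.
- **That the first round is an interim test of the primary outcome.** It concerns a named secondary outcome that is due for all patients by that date. The events overlap, but the 6-month endpoint itself is not tested.
- **That the trial needs an alpha adjustment for this look.** No stopping or adaptation rule is stated, and the simulation shows little effect.

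The coherent reading still does not remove the problem. It permits an early comparison on events that all feed the primary outcome while that outcome is accruing, in a single department with unblinded follow-up physicians and monthly meetings of all researchers. The point rests on two explicit statements and their timing; silence about access alone would not be a finding.

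**Conclusion.** The concern holds in limited form. The protocol excludes interim analyses and also schedules calculations that, naturally read, compare the arms on a subset of the primary-outcome events before follow-up ends. The 31 to 35 patients in step 2 apply only if the first round runs as soon as the last 1-month visit is in, and the lower range applies with a lag. The likely harm is biased referral, contact or event recording in those patients, plus an inaccurate statement in the report. The size of any such bias cannot be estimated from the document.

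The counts assume uniform accrual, enrolment close to discharge, and recruitment ending on the approximate date given. The lags and the 1-month event probabilities are assumptions. This should be corrected, but it does not undermine the validity of the 6-month test.

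**What to change.** Replace the sentence that sets two rounds of calculations with wording such as:

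> All between-arm comparisons, including those of the 1-month outcomes, will be made once, after the last 6-month visit and database lock. Before then, only pooled data-quality checks without arm labels will be made.

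This makes the ban on interim analyses true and leaves the endpoints and sample size unchanged. The cost is one sentence and a delay of about 5 months for the 1-month results (from about the end of April to about the end of September 2022).

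If the 1-month results are wanted earlier, the alternative is to declare the 1-month analysis as planned, remove the statement that there is no interim analysis, name who sees the results, and withhold them from treating and assessing staff until the last patient completes follow-up. This avoids the delay but requires control of access in a small single-department team.
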